## Abstract

**Background:**

Epilepsy is common in patients with a glioma. Antiepileptic drugs (AEDs) are the mainstay of epilepsy treatment, but may cause side effects and may negatively impact neurocognitive functioning and quality of life. Besides antiepileptic drugs, anti-tumour treatment, which currently consists of surgery, radiotherapy and/or chemotherapy, may contribute to seizure control as well. In glioma patients with seizure freedom after anti-tumour therapy the question emerges whether AEDs should be continued, particularly in the case where anti-tumour treatment has been successful. We propose to explore the possibility of AED withdrawal in glioma patients with long-term seizure freedom after anti-tumour therapy and without signs of tumour progression.

**Methods/Design:**

We initiate a prospective, observational study exploring the decision-making process on the withdrawal or continuation of AEDs in low-grade and anaplastic glioma patients with stable disease and prolonged seizure freedom after anti-tumour treatment, and the effects of AED withdrawal or continuation on seizure freedom. We recruit participants through the outpatient clinics of three tertiary referral centers for brain tumour patients in The Netherlands. The patient and the treating physician make a shared decision to either withdraw or continue AED treatment. Over a one-year period, we aim to include 100 glioma patients. We expect approximately half of the participants to be willing to withdraw AEDs. The primary outcome measures are: 1) the outcome of the shared-decision making on AED withdrawal or continuation, and decision related arguments, and 2) seizure freedom at 12 months and 24 months of follow-up. We will also evaluate seizure type and frequency in case of seizure recurrence, as well as neurological symptoms, adverse effects related to AED treatment or withdrawal, other anti-tumour treatments and tumour progression.

**Discussion:**

This study addresses two issues that are currently unexplored. First, it will explore the willingness to withdraw AEDs in glioma patients, and second, it will assess the risk of seizure recurrence in case AEDs are withdrawn in this specific patient population. This study aims to contribute to a more tailored AED treatment, and prevent unnecessary and potentially harmful use of AEDs in glioma patients.

## Background

Epilepsy is common in patients with primary malignant brain tumours, with incidence rates from 20 up to 90%, depending on tumour type, the location of the tumour and its proximity to the cortical gray matter [1]-[3]. The epileptogenicity of a tumour is inversely correlated with its growth rate [4]-[6]. Low-grade gliomas (LGGs), and particularly slow-growing tumours such as gangliogliomas and dysembryoblastic neuroepithelial tumours (DNETs), are the most epileptogenic [7]-[9]. A decrease in seizure frequency is known to contribute to less morbidity and improved quality of life [10],[11]. Therefore, achieving sustained seizure control in these patients is an important issue in brain tumour treatment.

Antiepileptic drugs (AEDs) are the mainstay of epilepsy treatment. However, AEDs may cause side effects and may also negatively impact neurocognitive functioning and quality of life [12]. Moreover, enzyme-inducing AEDs may interfere with chemotherapeutic drugs and corticosteroids and cause additional undesirable adverse effects [1],[13].

It is important to note that anti-tumour treatment, which currently consists of surgery, radiotherapy and/or chemotherapy, may contribute to seizure freedom as well. Retrospective studies on seizure control after surgical resection report seizure freedom after 6–12 months of follow-up in 63-75% of LGG patients [3],[14]-[18]. In a long-term follow-up study of patients with ganglioglioma of which 50% had refractory epilepsy, 85% reported sustained seizure freedom after 5 years [19]. Similar effects on seizure control are observed after radiotherapy or chemotherapy. In the EORTC phase III trial comparing early versus late radiotherapy in LGG patients, after radiotherapy 75% of patients were seizure free, compared to 59% of patients who had not been irradiated [20]. In several smaller series, after temozolomide chemotherapy a more than 50% seizure reduction was seen in 48-59% of LGG patients [21]-[26].

In patients with non-tumour-related epilepsy AEDs are generally discontinued some time after successful epilepsy surgery [18],[27],[28]. AED withdrawal following temporal lobe resection in patients with refractory non-tumoural epilepsy eventually leads to seizure freedom without use of AEDs in 77% of patients [29]. In a review on AED management after epilepsy surgery, AED withdrawal was associated with a lower rate of seizure recurrence compared to AED continuation. Moreover, in 77% of patients whose seizures recurred after AED withdrawal, seizure freedom could be regained after restart of medication [30]. After surgery for paediatric epilepsy, seizure freedom was achieved in 77% of patients who completed AED withdrawal during follow-up. Early AED withdrawal did not affect long-term seizure outcome [31]. In general, epileptologists recommend to start tapering after at least one year of seizure freedom after epilepsy surgery, although the exact timing of AED withdrawal is controversial [32]-[35].

In patients with seizure freedom after anti-tumour therapy the question emerges whether AEDs should be continued, particularly in the case where anti-tumour treatment has been successful. In addition, several studies suggest that the efficacy of AEDs in brain tumour patients is limited. Up to 50% of brain tumour patients still have seizures despite AED treatment [13],[36].

Seizure frequency is likely to increase without AED treatment in glioma patients with ongoing seizures, warranting continued treatment. However, the necessity of AEDs in glioma patients with long-term seizure control is disputable. A few studies support the notion that seizure freedom in brain tumour patients can be maintained without AEDs. In one series 45 out of 62 (73%) children with a brain tumour whose AEDs were withdrawn after anti-tumour treatment became seizure free [37]. Small observational studies on AED use in meningioma and LGG patients showed ongoing seizure freedom after AED withdrawal in a majority of patients [38]. In case seizures reoccur, they are often associated with tumour recurrence [38]. Larger observational studies show that AEDs often are unable to prevent seizure recurrence in patients with renewed tumour growth [16].

Altogether, both studies on seizure freedom after anti-tumour treatment and studies on seizure freedom after epilepsy surgery suggest that an attempt to withdraw AEDs is justified in glioma patients. Therefore, we propose to explore the possibility of AED withdrawal in low-grade and anaplastic glioma patients with long-term seizure freedom after anti-tumour therapy and without signs of tumour progression. As our study population consists of a carefully selected group of glioma patients, we aim to contribute to a more tailored AED treatment, and prevent unnecessary and potentially harmful use of AEDs in glioma patients.

## Methods/Design

### Design and overview

This is a prospective, observational study exploring the decision-making process on the withdrawal or continuation of AEDs in low-grade and anaplastic glioma patients with stable disease and prolonged seizure freedom after anti-tumour treatment, and the effects of AED withdrawal or continuation on seizure freedom. Over a one-year period, we aim to include 100 glioma patients, who will be followed for a duration of at least 24 months. We primarily aim to improve current knowledge on the patient’s and physician’s willingness to withdraw AEDs in brain tumour patients, and to identify the rate of successful AED withdrawals, i.e. that AED’s are withdrawn completely without seizure recurrence. We hypothesize that 1) approximately half of the participants will be willing to withdraw AEDs, and 2) that there will be no significant difference in seizure freedom at last follow-up between patients who have withdrawn and those who have continued their medication.

The study is approved by the institutional review board of the VU University Medical Center (registration number 2013/288).

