### Sample size

Based on the current population of patients with WHO grade I-III glioma with epilepsy receiving treatment in one of the three referral centers, we estimate that in one year a total of 100 patients will be eligible for this study. The number of patients who will actually withdraw their AEDs, will depend on the outcome of the shared decision-making process. Currently, there are no data on patients’ willingness to withdraw AEDs in this specific population. A retrospective study showed that in 42% of patients with intra-axial brain tumours AEDs were withdrawn after surgery as part of routine clinical practice, although patients on prophylactic AED treatment were also included in this analysis [38]. A cautious estimate is that at least 30 percent of the patients will be willing to withdraw AEDs. As this is an observational study that is not primarily aimed at exploring differences between the 2 groups, no formal sample size calculation can be made. A total number of 100 patients, with at least 30 patients in each group, should be sufficient to complete a prediction model, using 3 co-variates. We expect that less than 5% of the eligible patients are unwilling to participate, as this study is mostly part of routine clinical practice and because of the non-interventional character.

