Based on previous studies on seizure status after anti-tumour treatment or epilepsy surgery, we hypothesize that AEDs can be safely withdrawn in glioma patients who are seizure free and have shown no signs of tumour recurrence. However, we acknowledge that in glioma patients there still is a risk of seizure recurrence, as the epileptogenicity of the tumour may change over time, in particular when the tumour starts growing again [16],[17],[40],[41]. To reduce the risk of seizure recurrence, we will only include patients with clinically and radiologically stable disease and seizure freedom for at least 12 months after the last anti-tumour treatment. In addition, we will include patients who experienced seizures after anti-tumour treatment only after at least 24 months of seizure freedom. To ensure that patients will not be subjected to an unacceptably high risk of seizures, we will perform an interim analysis at the time the first 20 study patients who have withdrawn AEDs will have completed 12 months of follow-up. To prevent excess numbers of patients to be unnecessarily exposed to the intervention, the study will also end if none of the first 20 patients who are included decide to withdraw AEDs.

In summary, we present the design of a prospective observational study aimed at the development of a more targeted and well-considered AED treatment regimen in primary brain tumour patients with epilepsy, and at preventing possibly unnecessary treatment with AEDs. By closely monitoring the decision-making process on AED treatment and a subsequent observation of patient’s seizure status, we will gain more insight into both the willingness of patients and the safety of withdrawing AEDs in glioma patients with a presumably low risk of seizure recurrence. As we expect that AED can be safely withdrawn without substantially increasing the risk of seizure recurrence, this study may lower patients’ and physicians’ threshold to withdraw AEDs in glioma patients. The results of this study may eventually guide future recommendations concerning AED treatment in this specific patient population.

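### Hypothesis 2 predicts a non-significant group difference in seizure freedom, with no margin or interval criterion, so meeting it would not show that seizure freedom is similar

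*Protocol article*

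**What the plan says.** Design and overview gives two hypotheses. The first is that "approximately half of the participants will be willing to withdraw AEDs". The second is that "there will be no significant difference in seizure freedom at last follow-up between patients who have withdrawn and those who have continued" their medication. Seizure freedom at 12 and 24 months is one of the two primary outcomes (Primary outcome measures).

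On size and duration, the same section says "we aim to include 100 glioma patients, who will be followed for a duration of at least 24 months". The Sample size section adds a cautious estimate that "at least 30 percent of the patients will be willing to withdraw AEDs". It describes the study as observational and "not primarily aimed at exploring differences between the 2 groups, no formal sample size calculation can be made". It then justifies the number by the expected yearly count of eligible patients and by a model: 100 patients, "with at least 30 patients in each group, should be sufficient to complete a prediction model, using 3 co-variates".

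The Statistical analyses section covers descriptive statistics, univariate and multivariable logistic models, and an interim look. It names no between-group test, significance level or margin for hypothesis 2.

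The last paragraph of the Discussion looks ahead to the conclusion: "As we expect that AED can be safely withdrawn without substantially increasing the risk of seizure recurrence", the study may make patients and physicians readier to withdraw treatment.

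**The concern.** A hypothesis worded as absence of significance is met whenever a test fails to reject. Failure to reject becomes more likely as the study gets smaller or the data noisier. A non-significant result can come from two groups with the same seizure freedom or from too few patients to see a real difference, and the p-value alone does not separate the two. Only the estimate and its interval, set against a difference judged important, can do so.

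This matters because seizure freedom is a primary outcome and the Discussion expects the study to influence practice. If withdrawal did raise recurrence, a report that hypothesis 2 was confirmed could be taken as reassurance that the data do not provide.

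**Working it through.** **Plan's own figure.** There is no power-based figure to reproduce. The 100 is a feasibility count, and the only arithmetic behind 30 per group is 30 / 3 = 10 patients per covariate.

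**Inputs from the article.** Total 100 patients. The splits are 50/50 (the expectation in Design and overview) and 30 withdrawers to 70 continuers (the cautious estimate in Sample size).

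**Inputs that are assumed.**
- Two-sided level 0.05. The article gives no level for this comparison; its 0.10 thresholds are for variable selection.
- Recurrence in continuers, 10% to 30%. The article gives no figure and only describes the risk as presumably low.
- Recurrence in withdrawers about 1.8 to 2 times as high. In one setting this is 27%, the complement of the 73% (45 of 62) seizure-free in the cited series of children whose drugs were withdrawn. That series is paediatric and has no stated 24-month horizon, so 27% is a proxy and not an estimate for this population.
- No dropout. Losses would lower power.

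**Power.** Let x be recurrences among n1 withdrawers and y recurrences among n2 continuers. The test rejects when |x/n1 − y/n2| / √[p̄(1 − p̄)(1/n1 + 1/n2)] > 1.96, with p̄ = (x + y)/(n1 + n2). Power is the sum of the product binomial probabilities over all (x, y) that reject.

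**Precision.** Unadjusted 95% half-width = 1.96 × √[p1(1 − p1)/n1 + p2(1 − p2)/n2]. For 27% versus 15%:
- 50/50: 1.96 × √(0.1971/50 + 0.1275/50) = 1.96 × 0.0806 = 0.158
- 30/70: 1.96 × √(0.1971/30 + 0.1275/70) = 1.96 × 0.0916 = 0.180

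| Continuers vs withdrawers | Power 50/50 | Power 30/70 | Half-width 50/50 | Half-width 30/70 |
|---|---|---|---|---|
| 10% vs 20% | 30% | 30% | ±13.9 | ±16.0 |
| 15% vs 27% | 32% | 31% | ±15.8 | ±18.0 |
| 20% vs 36% | 43% | 40% | ±17.3 | ±19.6 |
| 25% vs 45% | 56% | 50% | ±18.3 | ±20.5 |
| 27% vs 51% | 71% | 63% | ±18.5 | ±20.7 |
| 30% vs 57% | 80% | 72% | ±18.7 | ±20.7 |

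Half-widths are in percentage points. The chance of a non-significant result is 100% minus the power:
- 15% vs 27%: 68% (50/50) and 69% (30/70)
- 20% vs 36%: 57% and 60%
- 25% vs 45%: 44% and 50%
- 27% vs 51%: 29% and 37%

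**Sensitivity to the level.** At two-sided 0.10, power for 15% vs 27% is 44% and 41%. For 20% vs 36% it is 56% and 51%, so at that level the point where a near-doubling is usually missed lies somewhat below 20%.

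**Events available for adjustment.** At 15% vs 27%, expected recurrences are 50 × 0.27 + 50 × 0.15 = 21.0, or 30 × 0.27 + 70 × 0.15 = 18.6. That is roughly 20.

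**The case against.** The strongest reply is that the study does not rest on this comparison. It is observational, the stated aims are willingness to withdraw and the rate of successful withdrawal (a within-group rate), and the Sample size section says that group differences are not the main aim. The Discussion bases its expectation of safety on previous studies and acknowledges that a risk of recurrence remains. The interim stopping rule does not use the comparison. All of this stands. It lowers the weight of the point but does not repair a hypothesis that remains one of two in the design and concerns a primary outcome.

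Three stronger readings are tempting, and the article does not support them.
- **That the plan will treat non-significance as proof of safety.** No section says so. It is an inference from reading the hypothesis beside the Discussion.
- **That the study would usually miss a near-doubling, without condition.** This holds at 0.05 only if recurrence in continuers is about 20% or less. At 25% or more, a near-doubling is detected at least about half the time. A presumably low risk fits the lower range, but the article gives no rate.
- **That the article is wrong to say no formal sample size calculation can be made.** An interval width at a fixed number of patients is a precision statement. It does not determine the number, and group sizes depend on patients' choices. Expected precision could usefully be added, but the sentence is not false.

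**Conclusion.** The wording of hypothesis 2 is unsound and should be changed. A non-significant difference with 30 to 50 withdrawers would not establish similar seizure freedom at any of the rates examined. Even in the setting of 27% versus 51%, 29% to 37% of studies would miss the difference.

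The size of the problem is conditional. At two-sided 0.05, with 100 patients and no losses, a near-doubling goes undetected in about 57% to 70% of studies when recurrence in continuers is 10% to 20%, and in about 29% to 50% at 25% to 27%. These figures rest on assumed rates and an assumed level. They are also unadjusted: the groups form by shared decision, so confounding limits a significant and a non-significant result alike.

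This is a should-fix point. No decision rule in the article depends on hypothesis 2, but the expected message for practice makes the wording consequential.

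**What to change.** 1. Replace hypothesis 2 with an estimation aim: the difference in 24-month seizure freedom, withdrawal decided minus continuation decided, with a two-sided 95% confidence interval.
2. State that a non-significant difference will not be read as evidence of equal seizure freedom or of safe withdrawal.
3. Allow a claim of no substantial increase in recurrence only if the interval excludes an excess that the investigators name in advance; otherwise report the result as inconclusive. The size of that excess is a clinical judgement for them to make.
4. In the Sample size section, add the expected unadjusted half-width under stated assumed rates: about ±14 to ±19 points at 50/50 and ±16 to ±21 at 30/70. Note that an adjusted difference will have its own precision, and that with roughly 20 recurrences (at 15% versus 27%) adjustment can cover only very few covariates.

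**Cost.** No extra patients and no change to treatment or follow-up. It needs redrafting and one clinical judgement made before the results are seen. The drawback is a weaker possible conclusion, because with these half-widths the study will probably be unable to exclude a moderate excess of recurrence. For illustration only, with equal true seizure freedom of 73% to 85%, 80% power and one-sided 0.025, n per group = (1.96 + 0.84)² × 2p(1 − p)/margin². This gives 51 (85%, 20-point margin) to 310 (73%, 10-point margin). Those margins are assumptions, as the article gives none.

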### Participants

#### Recruitment procedure

We recruit participants through the outpatient clinics of three of the largest tertiary referral centers for brain tumour patients in The Netherlands: one large community hospital (Medical Center Haaglanden, The Hague) and two university hospitals (VU University Medical Center, Amsterdam, and Erasmus MC Cancer Institute, Rotterdam). The three hospitals provide care for approximately one third of the Dutch primary brain tumour population.

One of the co-investigators ([name] and MK) will explore which patients are potentially eligible for inclusion and will maintain a log of every patient that has been approached to participate. The logs contain the patient’s initials, date of birth, date of screening, and whether the patient has given informed consent, and if not, the reason for non-participation. The co-investigator will inform the treating neuro-oncologists on eligible patients in their outpatients’ clinics. In case the treating neuro-oncologist thinks that AED withdrawal in that particular patient might have serious disadvantages (e.g. due to status epilepticus in medical history, high co-morbidity with recurrent seizures), that patient will not be approached to participate in the study, despite fulfillment of all eligibility criteria. This will be recorded separately.

All eligible patients in whom the physician has no serious objections against AED withdrawal will receive a patient information file. The treating neuro-oncologist will provide additional information and answer questions. Patients who decide to participate will be asked to give informed consent covering four topics: 1) to start the shared decision-making process with their treating physician on the withdrawal or continuation of AEDs and to subsequently implement the joint decision, 2) to collect relevant information from their medical records, 3) to follow-up their seizure status, where possible as a part of the regular out-patient clinic appointments, and 4) to inform other medical specialists or the patient’s general practitioner on the patient’s participation in the study.

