#### Primary outcome measures

The two primary outcome measures are: 1) the outcome of the shared-decision making on AED withdrawal or continuation, and decision related arguments, and 2) seizure freedom at 12 months and 24 months of follow-up.

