## Discussion

In this report, we describe the design of a prospective, observational study on the withdrawal of AEDs in low-grade and anaplastic glioma patients with prolonged seizure freedom. This study addresses two issues that are currently unexplored. First, it will explore the willingness to withdraw AEDs in glioma patients, and second, it will assess the risk of seizure recurrence in case in this specific patient population AEDs are withdrawn. Furthermore, risk factors for seizure recurrence including tumour progression will be studied.

Given the lack of clear evidence on the feasibility of AED withdrawal after anti-tumour treatment, there are – at this stage – serious ethical objections to the randomisation of patients. Moreover, in clinical practice most patients appear to have strong personal preferences for either withdrawal or continuation of AEDs. As a consequence, we have chosen an observational non-randomised study design. Unlike a randomised controlled study, the observational design allows us to explore the decision-making process with regard to AED treatment. As this study requires minimal additional efforts from the participants, we expect that most patients who are eligible for inclusion will be prepared to provide informed consent. In addition, the limited number of eligibility criteria will result in a high external validity of the study.

The participation of three of the largest referral centers for brain tumour patients contributes to the strength of this study, as this allows us to reach a substantial part of all Dutch low-grade and anaplastic glioma patients. As a consequence of the involvement of patients in the decision-making process, this study is in accordance with current clinical practice.

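### The study aims to measure physicians' willingness to withdraw AEDs, but patients whose physician seriously objects never enter the willingness outcome, and no section brings them back into the result

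*Protocol article*

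**What the plan says.** **Aim.** Design and overview states: "We primarily aim to improve current knowledge on the patient’s and physician’s willingness to withdraw AEDs in brain tumour patients". The same section hypothesises that about half of the participants will be willing to withdraw.

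**Outcome.** Under Primary outcome measures, the first outcome is "the outcome of the shared-decision making on AED withdrawal or continuation, and decision related arguments".

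**Filter.** Recruitment procedure places a physician judgement before approach and consent. If the treating neuro-oncologist thinks withdrawal might have serious disadvantages, "that patient will not be approached to participate in the study, despite fulfillment of all eligibility criteria". It continues: "All eligible patients in whom the physician has no serious objections against AED withdrawal will receive a patient information file".

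**Records.** The recruitment log covers approached patients only: the co-investigator "will maintain a log of every patient that has been approached to participate". For patients held back by the physician, the text says "This will be recorded separately". It does not say what that record contains. Under Intervention, the patient's or physician's reasons for continuing are recorded when participants decide against withdrawal.

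**Generalisation.** The Discussion states that "the limited number of eligibility criteria will result in a high external validity of the study". The physician filter is not mentioned there.

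**The concern.** The filter selects patients on one of the quantities that the study sets out to measure. A physician who seriously objects to withdrawal in an eligible patient is giving the plainest possible evidence of unwillingness. That evidence falls outside the first primary outcome because the patient is never approached.

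Three results are affected when read as statements about eligible glioma patients in general:

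- the withdrawal proportion;
- the physician's side of willingness;
- the tabulated arguments for continuing, together with the planned regression on the decision to withdraw. The examples given for the filter (earlier status epilepticus, high co-morbidity with recurrent seizures) are likely to be among the weightiest physician arguments, and they will be thin or absent among participants.

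The external-validity statement adds to this. It rests on the small number of eligibility criteria, whereas recruitment also applies an open-ended discretionary exclusion on top of them.

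**Working it through.** **Inputs from the protocol article**

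- Hypothesised withdrawal rate among participants: about 50% (Design and overview).
- Cautious rate: at least 30% (Sample size).
- Planned number: 100 (Design and overview; Sample size).
- Share of criteria-eligible patients excluded by the physician, v: not given. Values of 5% to 30% are assumed below to show the range.

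**The plan's own figure.** There is no formal sample size calculation to reproduce. The stated minimum of 30 withdrawals follows from the cautious rate: 0.30 × 100 = 30.

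**Formula.** Let w be the withdrawal rate among participants. Patients excluded by the physician are taken to continue AEDs, and patient refusals are left out. Then

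rate among all criteria-eligible = w × (1 − v).

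The participant rate therefore exceeds the all-eligible rate by a factor 1/(1 − v). This is never below 1, so the difference has only one direction. The same factor applies to the share of patients whose physician supports withdrawal.

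**Results**

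| Assumed v | All-eligible rate if w = 50% | All-eligible rate if w = 30% | Factor 1/(1 − v) | Patients excluded if 100 are enrolled, 100/(1 − v) − 100 |
|---|---|---|---|---|
| 5% | 47.5% | 28.5% | 1.05 | 5.3 |
| 10% | 45% | 27% | 1.11 | 11.1 |
| 20% | 40% | 24% | 1.25 | 25.0 |
| 30% | 35% | 21% | 1.43 | 42.9 |

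**Scale against sampling error.** The Wilson 95% interval for 50 of 100 is 40.4% to 59.6%. The all-eligible rate falls below the lower limit when 0.50 × (1 − v) < 0.404, that is when v > 1 − 0.404/0.50 = 0.192. Below about 19% exclusion, the shift is smaller than the sampling uncertainty of the participant rate; above that it is larger.

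**Is the separate record used?** Primary outcome measures, Descriptive statistics, Univariate analysis and Multivariable analysis do not mention it. Sample size allows for fewer than 5% of eligible patients declining to take part and says nothing about physician exclusions.

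**The case against.** The strongest case on the other side has five parts.

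- **The hypothesis concerns participants.** For them the rate is not biased. This stands, and the point is worded accordingly. The stated aim and the external-validity claim are wider than the hypothesis, and the mismatch lies there.
- **The exclusions are recorded.** A reader might infer that the filter makes an overstated result unavoidable. The text does not support that: with a count of physician exclusions, the all-eligible rate can be rebuilt. What remains is that no section says it will be, and that a reason for each exclusion is not stated to be kept.
- **Physician reluctance is still measured.** Only serious objections are filtered out, and lesser ones are recorded among participants. This also stands. It limits the loss to the strongest objections, which are also the most informative ones.
- **A condensed article leaves reporting detail to the full protocol or SAP.** That is fair for the layout of tables. Here the article's own aim, recruitment rule and external-validity claim do not fit together. The article does call its population carefully selected, with a presumably low recurrence risk, but the external-validity sentence does not carry that limit.
- **Patients never approached had no shared decision.** Recoding them inside the first primary outcome would mix a one-sided physician judgement with a joint one. This is a good argument against redefining the outcome, and the fix does not do so.

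A reader might also infer that the seizure-recurrence estimate is biased in the same way. The point does not extend to it: patients whose physician seriously objects would be expected to continue AEDs, so adding them to a denominator leaves recurrence after withdrawal unchanged. Nor can a shortfall below 30 withdrawals be claimed, because the article does not say whether its 100 eligible patients are counted before or after the filter.

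**Conclusion.** The concern holds in a limited form. The first primary outcome cannot by itself answer the stated aim about physicians' willingness, because eligible patients with a serious physician objection are removed before it is observed. Relative to all patients meeting the eligibility criteria, and only relative to them, the withdrawal proportion and physician willingness are too high by 1/(1 − v).

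The size cannot be derived from the documents. At a participant rate of 50%, the gap is 5 percentage points at an assumed v of 10% and 10 points at 20%. These figures assume that every excluded patient continues AEDs, and they ignore refusals. If few patients are excluded, the effect is minor beside sampling error. The protocol offers no basis for saying which case applies, which is itself a reason to report the number. The external-validity statement is too broad as it stands.

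**What to change.** 1. Keep the shared-decision outcome among participants as the first primary outcome. Beside it, report the withdrawal proportion over all patients who meet the eligibility criteria, with physician exclusions shown as physician-decided continuation and patient refusals as a separate category.
2. State that an anonymised reason is recorded for each physician exclusion, and tabulate these reasons alongside the decision-related arguments from participants.
3. In the Discussion, limit the external-validity statement to eligible patients whose physician had no serious objection to withdrawal.

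The clinical filter is not altered. The cost is a lower willingness figure shown beside the participant rate, plus one recorded item per excluded patient if the separate record does not already hold the reason.
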